#### Clinical vaccine efficacy

***Primary endpoint***

*Time to first episode of clinical malaria during the six-month efficacy follow-up period using the primary case definition* – The logrank statistic and corresponding p‑value will be calculated to test the null hypothesis of no difference in the distribution of time to clinical malaria between the FMP1/AS02A and rabies vaccine groups. A Cox proportional hazards model with an indicator variable for vaccine group will be fit to the data and an estimate of the hazard ratio along with its corresponding 95% confidence interval will be computed. Vaccine efficacy will be defined as one minus the hazard ratio. Additional Cox models may explore the effects of age, sex, bed net use as reported at baseline, nearest field station, and hemoglobin genotype on vaccine efficacy. Kaplan-Meier curves for time to clinical malaria will be generated by vaccine group. An alternative estimate of vaccine efficacy based on cumulative incidence rates will be calculated as well.

The primary data analysis will be conducted with the ATP cohort; however, a similar analysis based on the ITT cohort will be performed to assess the robustness of the analysis based on the ATP cohort.

***Secondary endpoints***

*Time to first episode of clinical malaria during the six-month efficacy follow-up period using the secondary case definitions in Exhibit 8 –* Similar analyses as those outlined for the primary endpoint will be carried out for these endpoints.

*Number of clinical episodes of malaria per subject during the six-month efficacy follow-up period using the primary case definition* – Statistical methods for recurrent event data, such as Poisson regression, will be used to assess the effect of FMP1/AS02A vaccination on the average number of clinical episodes per subject. A table of the frequency of clinical episodes by vaccine group will be generated.

*Number of clinical episodes of malaria per subject during the six-month efficacy follow-up period using the secondary case definitions in Exhibit 8* – Similar analyses as those conducted for the number of episodes using the primary case definition will be carried out.

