### Secondary Endpoints

Because this is a Phase IIb trial, it has many secondary endpoints. Their purpose is to gain insight into the efficacy of the vaccine and to help define a primary endpoint for a confirmatory Phase III trial. They are not intended for use to make formal claims about the vaccine.

Measurements of efficacy during the EFP:

- Times to clinical episode of *P. falciparum* malaria meeting the various secondary case definitions shown in Exhibit 8
- Time to presence of asexual stage *P. falciparum* parasites during the six-month efficacy follow-up period
- Time to parasite density  50,000 asexual stage *P. falciparum* parasites per microliter of blood during the six-month efficacy follow-up period
- Number of clinical episodes of malaria, per subject, meeting the primary case definition
- Presence of MSP-1 3D7 parasites in clinical cases of malaria meeting the primary case definition
- Presence of MSP-1 3D7 parasites at a given cross-section survey time
- Time to anemia defined as Hgb < 8.0 g/dl, whether by active or passive case detection
- Proportion of subjects with anemia (Hgb < 8.0 g/dl)

Safety during the EFP:

- Occurrences of solicited AEs during a seven‑day follow-up period (vaccination day and six subsequent days) after each vaccination (five visits: vaccination day and days 1, 2, 3, and 6)
- Occurrences of unsolicited AEs during a 30-day follow-up period after each vaccination (vaccination day and 29 subsequent days)
- Occurrences of SAEs between the first vaccination and the end of the EFP

Immunogenicity during the EFP:

- Geometric means of MSP-1 Ab titers at Visits 2, 7, 12, 17, 20, and 23 (o/a Study Days 0, 29, 57, 85, 171, and 256)

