## Sample Size

Preliminary results from the WRAIR #1020 epidemiological study indicate that approximately 50% of children experienced at least one episode of clinical malaria in the first six months of follow-up. In this analysis, clinical malaria is defined as a parasite density  50,000 parasites per microliter in the presence of fever (axillary temperature  37.5 C). If one assumes that time to clinical malaria follows an exponential distribution, a 50% cumulative incidence rate corresponds to a hazard rate of 0.1155/month. A trial with 200 subjects per study arm, therefore, will have roughly 80% power to detect a 38% reduction in this hazard rate. A 38% reduction in the hazard rate corresponds to a 30% reduction in the six-month cumulative incidence rate. In terms of time to event, these rates imply that 25% of the subjects in the comparator group are expected to contract malaria within about 2.5 months from the third immunization; the comparable time for the FMP1/AS02A arm will be roughly 4 months. The median time to first clinical episode is expected to be 6 months and 10 months, respectively.

This sample size calculation is based on a two-sided 0.05-level logrank test. It assumes that children receive 3 doses of vaccine and then are followed for 6 months after the third dose. Cases of malaria are counted after the third dose of vaccine. Twenty percent of children are assumed to dropout during the immunization period. No further dropouts are assumed during the efficacy follow-up period.

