## Final analyses

This section describes the analyses planned for the primary and secondary endpoints as well as for the most important of the tertiary endpoints. A Reporting and Analysis Plan (RAP) will be prepared before all subjects reach SD 240 and the study is partially unblinded. The RAP will describe the data analyses in fuller detail.

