***Tertiary endpoints***

*Time to first episode of clinical malaria during the ten-month efficacy follow-up period using the primary case definition* – Similar analyses as those outlined for the primary endpoint will be carried out for this endpoint. In addition, Cox proportional hazards models with time-dependent covariates reflecting the various follow-up periods will be fitted to the data to assess whether vaccine efficacy changes with time.

*Time to first clinical episode of malaria during the ten-month efficacy follow-up period using the secondary case definitions* – Similar analyses as those outlined for the primary endpoint will be carried out for these endpoints. In addition, Cox proportional hazards models with time-dependent covariates reflecting the various follow-up periods will be fitted to the data to assess whether vaccine efficacy changes with time.

*Number of clinical episodes of malaria per subject during the ten-month efficacy follow-up period using the primary case definition* – Similar analyses as those proposed for number of episodes meeting the primary case definition during the six-month efficacy follow-up period will be conducted.

*Number of clinical episodes of malaria per subject during the ten-month efficacy follow-up period using the secondary case definitions* – Similar analyses as those proposed for the number of episodes meeting the primary case definition during the ten-month efficacy follow-up period will be conducted.

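### Poisson regression is the only method named for repeat malaria episodes, with no provision for differences in risk between children; used with model-based standard errors, its intervals would be too narrow if such differences exist

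*Protocol*

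**What the plan says.** Under the secondary endpoints of section 12.4.2 (Clinical vaccine efficacy), the protocol states: "Statistical methods for recurrent event data, such as Poisson regression, will be used to assess the effect of FMP1/AS02A vaccination on the average number". The quantity meant is each child's episode count under the primary case definition, over the six-month efficacy follow-up period. For the secondary case definitions of Exhibit 8 it adds: "Similar analyses as those conducted for the number of episodes using the primary case definition will be carried out". For ten months, under the tertiary endpoints, it says: "Similar analyses as those proposed for number of episodes meeting the primary case definition during the six-month efficacy follow-up period will be conducted", and the secondary definitions follow in the same way. One named example therefore serves six clinical case definitions over two periods.

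No robust variance, dispersion parameter, negative binomial model or frailty term is mentioned. Age, sex, bed net use, nearest field station and hemoglobin genotype are recorded at baseline (footnotes to Exhibit 7). They are offered as optional covariates for Cox models of the primary endpoint, but are not mentioned for the counts.

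Two other statements set the weight of the point. Section 12.4 defers detail to the Reporting and Analysis Plan (RAP): "The RAP will describe the data analyses in fuller detail". Section 12.1.2 says of the secondary endpoints: "They are not intended for use to make formal claims about the vaccine". It also gives them the task of helping to define the primary endpoint of a Phase III trial.

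**The concern.** Poisson regression with vaccine group as its only predictor, and with model-based standard errors, takes the variance of a child's count to equal its mean. That holds if all children in an arm share one rate over the same time at risk. If some children are persistently at higher risk than others, the variance exceeds the mean and the model-based standard error of the log rate ratio is too small.

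The protocol gives reasons to expect unequal risk. Children are 12 to 47 months old, section 4.2 says that malaria weighs most on the younger age groups, and the listed covariates are there because they may matter.

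At stake is the comparison between candidate Phase III endpoints. If intervals for episode counts are falsely narrow while those for time to first episode are sound, the count endpoint looks more sensitive than it is.

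**Working it through.** **The protocol's own figure.** Section 12.3 states that "approximately 50% of children experienced at least one episode of clinical malaria in the first six months of follow-up", that "This sample size calculation is based on a two-sided 0.05-level logrank test", and that "A trial with 200 subjects per study arm, therefore, will have roughly 80% power to detect a 38% reduction in this hazard rate". The control hazard is ln 2 / 6 = 0.1155 per month. With 20% dropout during immunization, 160 children per arm remain. At a hazard ratio of 0.62, the six-month incidence is 0.500 and 1 − 0.5^0.62 = 0.349. Expected events are 160 × (0.500 + 0.349) = 135.9. Schoenfeld's formula gives power Φ(√(135.9/4) × |ln 0.62| − 1.96) = 79.6%, so the stated figure is reproduced. It concerns first episodes and uses no Poisson count variance, so the present point does not touch it.

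**Model for repeat episodes.** The document gives no dispersion of episode counts, so theta is assumed here. Let a child's count be Poisson with mean mu × g, where g is gamma distributed with mean 1 and variance theta. Then:

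- Variance of a count = mu + theta × mu², so variance / mean = 1 + theta × mu.
- P(no episode) = (1 + theta × mu)^(−1/theta). Setting this to 0.5, to keep the protocol's 50%, gives 1 + theta × mu = 2^theta and mu = (2^theta − 1)/theta.
- With no vaccine effect, true standard error / Poisson standard error = √(1 + theta × mu) = 2^(theta/2). This does not depend on the number of children.
- Actual two-sided type I error = 2 × P(Z > 1.96 / 2^(theta/2)).

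| theta (assumed) | mu | variance / mean | standard error too small by | type I error | coverage of nominal 95% interval |
|---|---|---|---|---|---|
| 0 | 0.69 | 1.00 | 1.00 | 5.0% | 95% |
| 0.25 | 0.76 | 1.19 | 1.09 | 7% | 92.8% |
| 0.5 | 0.83 | 1.41 | 1.19 | 9.9% | 90.1% |
| 1 | 1.00 | 2.00 | 1.41 | 16.6% | 83.4% |
| 2 | 1.50 | 4.00 | 2.00 | 32.7% | 67.3% |

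**Check by simulation** (160 per arm, 20,000 trials per setting, no vaccine effect). Plain Poisson rejected in 5.0%, 9.9%, 16.5% and 32.4% of trials at theta 0, 0.5, 1 and 2. Poisson with a robust standard error rejected in 5.0% to 5.5% in every setting.

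**What it does to an interval.** Take a rate ratio of 0.62, theta 1 and control mean 1.0. The Poisson variance of the log rate ratio is 1/160 + 1/(160 × 0.62) = 0.0163, standard error 0.128. Adding 2 × theta/160 = 0.0125 gives 0.0288, standard error 0.170. The 95% interval for efficacy is 20% to 52% with plain Poisson and 14% to 56% with the extra variance included.

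**Other definitions.** The 50% applies to the primary definition over six months. Because the ratio is 1 + theta × mu, the error shrinks for rarer definitions and grows for commoner ones. If 15% of children had an episode (an assumption) at theta 1, mu would be 1/0.85 − 1 = 0.176 and the type I error about 7%.

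**The case against.** The strongest reply is that the protocol does not fix the faulty analysis. It commits to a class of recurrent-event methods and gives Poisson regression as an example. The Andersen-Gill model belongs to that class and could be used without an amendment. The variance estimator is ordinary RAP content, and the RAP is due before partial unblinding and goes to the DSMB for approval (section 13.3.2). Poisson regression with a robust per-child variance is also valid, as the simulation shows, so the model itself is not the fault. All of this stands. It makes the point a request about wording rather than a demonstrated error.

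It also stands that overdispersion is not shown. Seasonal change common to all children does not by itself create it, and a protected interval after treatment could offset some of it. The planned table of episode frequencies by group would help to reveal it.

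The reply does not remove the point. The only method named is the one that most needs a qualification, and it is passed by reference to every definition at both time points.

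A reader might also infer that repeat contacts within one illness will be counted again and inflate the clustering, because Exhibit 8 gives no rule for separating episodes. The documents do not support a claim of that size. The primary definition needs documented fever together with a density at or above its threshold, symptomatic cases are treated the same day, and section 12.4.2 already adjusts time at risk for antimalarial use. What remains is a missing detail with no figure attached.

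**Conclusion.** The point holds in conditional form and is minor. If the named method is used with model-based standard errors, and if children differ in underlying risk, the intervals for episode counts are too narrow. The understatement of the standard error runs from a factor of about 1.09 at theta 0.25 to 2.0 at theta 2, and it vanishes at theta 0. These figures rest on an assumed gamma distribution, assumed values of theta and the protocol's 50% for the primary definition.

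Two stronger readings go too far. One is that the protocol prescribes plain Poisson and that the counts are known to be overdispersed; neither is stated. The other is that a false significant result becomes likely. Over the assumed range the error rate is 7% to 33%, so such a result becomes more likely than 5%, but not likely. Trial success depends only on the logrank test of first episodes (section 5.4), and the secondary endpoints carry no formal claims. The practical consequence is confined to how these endpoints inform the choice of a Phase III endpoint.

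**What to change.** In section 12.4.2, or in the RAP before partial unblinding, replace the Poisson example with a method that allows for variation between children: negative binomial regression, or Poisson regression or the Andersen-Gill model with robust per-child variance. Enter log time at risk as the offset in the count models; Andersen-Gill handles time at risk through its risk sets. State that this applies to all case definitions at six and ten months.

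As a secondary wording point, the RAP should say how one episode is separated from the next for counting. That rule should agree with the time-at-risk adjustment for antimalarial use already in section 12.4.2.

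The cost is one clause and wider intervals where children do differ. Where they do not, little is lost: with theta 0 the robust version rejected in about 5.2% of simulated trials.

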***Tertiary endpoints***

*Time to first episode of clinical malaria during the ten-month efficacy follow-up period using the primary case definition* – Similar analyses as those outlined for the primary endpoint will be carried out for this endpoint. In addition, Cox proportional hazards models with time-dependent covariates reflecting the various follow-up periods will be fitted to the data to assess whether vaccine efficacy changes with time.

*Time to first clinical episode of malaria during the ten-month efficacy follow-up period using the secondary case definitions* – Similar analyses as those outlined for the primary endpoint will be carried out for these endpoints. In addition, Cox proportional hazards models with time-dependent covariates reflecting the various follow-up periods will be fitted to the data to assess whether vaccine efficacy changes with time.

*Number of clinical episodes of malaria per subject during the ten-month efficacy follow-up period using the primary case definition* – Similar analyses as those proposed for number of episodes meeting the primary case definition during the six-month efficacy follow-up period will be conducted.

*Number of clinical episodes of malaria per subject during the ten-month efficacy follow-up period using the secondary case definitions* – Similar analyses as those proposed for the number of episodes meeting the primary case definition during the ten-month efficacy follow-up period will be conducted.

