## Tertiary

The tertiary objectives pertain to the Addendum Efficacy Follow-up Period (AEFP).

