***Efficacy and Exploratory***

- To assess the efficacy of the FMP1/AS02A malaria vaccine against clinical episodes of *P. falciparum* malaria
- To assess the biological effects of the FMP1/AS02A malaria vaccine

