### Tertiary Endpoints

This study has many tertiary endpoints. As with the secondary endpoints, their purpose is to gain further insight into the performance of the vaccine.

Measurement of safety (during the EFP and Addendum Efficacy Follow-up Period [AEFP]):

- Occurrences of SAEs between the first vaccination and the end of the study

Measurement of immunogenicity (during the EFP and AEFP):

- Geometric means of MSP-1 Ab titers at Study Days 0, 29, 57, 85, 171, 256, and 340

Measurement of efficacy and other biological effects by either active or passive detection (during the AEFP unless otherwise noted):

- Times to first clinical episode of *P. falciparum* malaria meeting the primary case definition (EFP and AEFP combined)
- Times to first malaria episode of *P. falciparum* malaria meeting the secondary case definitions in Exhibit 8 (EFP and AEFP combined)
- Time to presence of asexual stage *P. falciparum* parasites (EFP and AEFP combined)
- Time to parasite density  50,000 asexual stage *P. falciparum* parasites per microliter of blood (EFP and AEFP combined)

Number of clinical *P. falciparum* malaria episodes, per subject, meeting the primary case definition (EFP and AEFP combined)

- Presence of MSP-1 3D7 parasites in clinical cases of malaria meeting the primary case definition (EFP and AEFP combined)
- Presence of MSP-1 3D7 parasites at a given cross-section survey time (EFP and AEFP combined)
- Vaccine-induced GIA activity
- The parasite density at each episode of malaria infection meeting the primary and secondary definitions of clinical malaria and infection (see Exhibit 8)
- *P. falciparum* malaria allele types per malaria episode, meeting the primary and secondary definitions of clinical malaria and infection (see Exhibit 8)
- Times to first observation of anemia (Hgb < 8.0 g/dl), whether by active or passive case detection (EFP and AEFP combined)
- Hgb levels at all scheduled points of collection
- Proportion of subjects with anemia (Hgb < 8.0 g/dl) at each study collection
- Proportion of subjects with a documented decline in Hgb level of ≥ 20%
- Proportion of subjects with anemia (Hgb < 8.0 g/dl) at last study collection
- Number of cases of documented decline in Hgb level from baseline to last study sample collection
- Parasite density at all scheduled points of collection
- Non-3D7 parasite densities at all scheduled points of collection
- Genotyping for multiplicity of infections
- Antibody against fragments of MSP-142

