### Analysis of Test Article Efficacy

The effect of FMP1/AS02A on clinical and biological endpoints will be analyzed as outlined below. For time-to-event analyses based on the six-month efficacy follow-up period, time is measured from 14 days after administration of the third dose of study vaccine (SD 71). Subjects will be censored at the time they become lost to follow-up or at the end of the efficacy follow-up period (SD 240), whichever occurs first. Loss to follow-up will also reflect death and moving away from the study area. Adjustments to time at risk will be made for anti-malarial usage and temporary absence from Kombewa. For time-to-event analyses based on the ten-month efficacy follow-up period, time will be measured from 14 days after administration of the third dose of vaccine. Subjects will be administratively censored at SD 364. For time-to-event-analyses based on the ITT cohort, time is measured from time of randomization (SD 0).

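### The tertiary objective asks for efficacy during the AEFP, but no planned clinical-episode analysis isolates that period without dropping children who already had an episode

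*Protocol*

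**What the plan says.** Section 5.3 opens with "The tertiary objectives pertain to the Addendum Efficacy Follow-up Period (AEFP"), and its efficacy item is "To assess the efficacy of the FMP1/AS02A malaria vaccine against clinical episodes of" *P. falciparum* malaria. The Summary repeats that item with the AEFP named as the period.

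Section 12.1.3 heads its efficacy and biological endpoints "during the AEFP unless otherwise noted", and then notes otherwise for each endpoint that times or counts clinical episodes. Time to first episode is for "malaria meeting the primary case definition (EFP and AEFP combined"), the secondary case definitions are treated alike, and the count is of "malaria episodes, per subject, meeting the primary case definition (EFP and AEFP combined").

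Section 12.4.2 says that for the ten-month analyses "time will be measured from 14 days after administration of the third dose of vaccine", with administrative censoring at SD 364. Two kinds of tertiary analysis follow:

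- Time to first episode over ten months, analysed like the primary endpoint, plus Cox models with time-dependent covariates for the follow-up periods. These "will be fitted to the data to assess whether vaccine efficacy changes with time".
- Number of episodes per subject over ten months, analysed by recurrent-event methods such as Poisson regression. No split by period is given.

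Section 12.3 bases the sample size on an epidemiological study in which "approximately 50% of children experienced at least one episode of clinical malaria in the first six months of follow-up".

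**The concern.** The objective asks what the vaccine does between SD 240 and SD 364. The pooled analyses answer a different question: what it does from SD 71 to SD 364. First episodes cluster early, so a pooled first-episode result leans on EFP data and could look favourable even if protection had gone by SD 240.

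The period Cox models do yield an AEFP estimate, but only among children who came through the EFP without an episode. If the vaccine works, more vaccinees than controls do so. If children also differ in underlying risk, the controls who remain are a more strongly selected low-risk group than the vaccinees who remain. The two groups are then no longer comparable as randomised, and the hazard ratio moves towards 1 with no loss of protection in any child. Section 12.4.2 itself names age, bed net use, nearest field station and hemoglobin genotype as factors to explore, so differing risk is plausible.

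At stake is whether the extra four months of follow-up answer the objective set for them.

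**Working it through.** **Inputs.** Section 12.3: 200 per arm, 20% dropout during immunisation and none afterwards (160 per arm enter the EFP), 50% control incidence in six months, hazard 0.1155/month, 38% hazard reduction (HR 0.62), two-sided 0.05 log-rank test. Section 6.1: EFP 169 days. SD 240 to SD 364 is 124 days, so SD 71 to SD 364 is 293 days.

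**The plan's own figure.** Control incidence is 0.50. Vaccine incidence is 1 − 0.5^0.62 = 0.349. Expected events are 160 × (0.500 + 0.349) = 135.9. Schoenfeld: √135.9/2 × |ln 0.62| − 1.96 = 0.83, which gives 79.6% power. The stated 80% reproduces.

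**EFP share of pooled first episodes.** The same hazards are extended to 10 months, or to 6 × 293/169 = 10.4 months on the day scale.

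| | EFP | AEFP, to 10 months | AEFP, to 10.4 months |
|---|---|---|---|
| Control | 80.0 | 29.6 | 31.9 |
| Vaccine | 55.9 | 25.9 | 28.2 |
| Total | 135.9 | 55.5 | 60.0 |

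The EFP share is 135.9/191.4 = 71% or 135.9/195.9 = 69%. If efficacy were 38% in the EFP and zero in the AEFP, the large-sample pooled Cox estimate would still be about 27% (HR 0.73). For all episodes at a constant rate, the EFP share would be 169/293 = 58%.

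**Who enters the AEFP term of the first-episode Cox model.** Controls: 160 × 0.50 = 80. Vaccinees: 160 × 0.5^0.62 = 104. With 55.5 to 60.0 events, Schoenfeld power for HR 0.62 is 43% to 46%.

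**Possible false waning.** Assumption: each child's risk carries a gamma factor with mean 1 and variance θ. The protocol gives no value, so a range is shown. Control incidence is fixed at 50% by SD 240 and the within-child hazard ratio is 0.62 throughout. The marginal hazards are λ/(1 + θλt) for controls and 0.62λ/(1 + 0.62θλt) for vaccinees, with λ = (0.5^(−θ) − 1)/(6θ). The Cox score equation was solved over each period, and again with the clock restarted at SD 240 for all children.

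| θ | EFP efficacy | AEFP, first episodes | AEFP, clock restarted |
|---|---|---|---|
| 0 | 38% | 38% | 38% |
| 0.25 | 36% | 33% | 37% |
| 0.5 | 34% | 28% | 35% |
| 1 | 31% | 21% | 32% |
| 2 | 25% | 11% | 27% |

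The false drop is thus about 3 to 14 points, and none under homogeneous risk. The last column assumes that earlier episodes do not alter later risk.

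**Size against noise.** The standard error of the change in log hazard ratio is about √(1/80 + 1/55.9 + 1/31.9 + 1/28.2) = 0.31. For θ = 0.5, 1 and 2 the false changes are 0.09, 0.14 and 0.18, or about 0.3 to 0.55 standard errors. A two-sided 5% test of change would then reject about 6% to 9% of the time.

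**Events if all children re-enter at SD 240.** Over 6 × 124/169 = 4.40 months at the protocol's hazards and with no further dropout: 160 × (1 − e^(−0.1155 × 4.40)) = 64 controls and 160 × (1 − e^(−0.62 × 0.1155 × 4.40)) = 43 vaccinees, about 107 in all. That is more than the 60 in the first-episode AEFP term and fewer than the 196 in the pooled analysis.

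**The case against.** The other side has several good points.

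- A reader might infer that the tertiary endpoints use first episodes only. They do not: Sections 12.1.3 and 12.4.2 also plan episode counts over ten months. What remains is that those counts are pooled.
- A reader might infer that every AEFP result is mostly EFP data. That holds for the pooled first-episode test and hazard ratio. The period term of the Cox model uses AEFP events, and the pooled estimate would move from 38% to about 27% if AEFP efficacy were zero.
- The false decline depends on a real vaccine effect and on heterogeneity that the protocol does not quantify. It is well under one standard error, so a false report of waning would be little more likely than by chance.
- Restarting the clock is not free of difficulty. If the vaccine works, the arms reach SD 240 with different histories of malaria and antimalarial treatment, which may influence later risk.
- Tertiary endpoints are for insight, and success under Section 5.4 rests on the EFP alone.
- Section 12.4 leaves fuller detail to a Reporting and Analysis Plan, which could add a period term.

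The last point carries only so far. The endpoint windows, the clock and the method for assessing change over time are fixed in the protocol, and they do not match its own objective.

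**Conclusion.** The mismatch stands on the text and needs no assumption: the objective is confined to the AEFP, the clinical-episode endpoints are not, and the only analysis by period conditions on freedom from an earlier episode. That about 70% of pooled first episodes fall in the EFP, and that about 80 against 104 children remain at risk at SD 240, follows from the Section 12.3 hazards held constant to SD 364.

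The drift towards no effect is a possibility of unknown size: 3 to 14 points for assumed variances of 0.25 to 2, and zero if risk is homogeneous. The documents do not support the stronger conclusion that a working vaccine would be reported as waning. They give no measure of heterogeneity, and the drift is small beside the standard error of 0.31.

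This is a worthwhile, low-cost improvement to a tertiary analysis. The primary analysis and the success criterion are untouched.

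**What to change.** In Sections 12.1.3 and 12.4.2:

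- Add an AEFP-specific analysis by randomised arm: time from SD 240 to the next episode meeting the primary case definition, in all children still under follow-up at SD 240 whatever their earlier episodes, with log-rank test and Cox model as for the primary endpoint.
- Add a vaccine-by-period term to the recurrent-event model already planned, and base the assessment of change in efficacy mainly on it.
- Keep the pooled ten-month analysis and the first-episode period Cox models as supportive, the latter with a stated caveat on selection.

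The cost is a few lines of text and additional analyses of data already collected. The AEFP estimate will have fewer events and a wider interval than the pooled one. The text should also say that the restarted estimate is a total effect, which includes any influence of earlier episodes or antimalarial treatment on later risk.
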